### Shared decision-making aid

The shared decision-making aid for AOM was developed and validated through observation of clinical care encounters, surveys of parents whose child recently had an ear infection, and interviews with parents [43]. The tool has been demonstrated to be patient-centered and have high internal and external validity. To further refine this tool, use of the shared decision-making aid will be recorded for observation by the research team during encounters with ten children with AOM. The findings will inform the adaptation of the aid along with input from a stakeholder advisory committee of parents, clinicians, and administrators to ensure the aid meets the needs of diverse patients and is easy to use for both parents and clinicians. The aid will be adapted for use on a webpage (current form) and on paper. The process of aid adaptation will align with the International Patient Decision Aid Standards [44, 45].

### Evaluation with RE-AIM including data analytics plan

The Reach Effectiveness Adoption Implementation Maintenance (RE-AIM) [34] framework will guide the evaluation of implementation outcomes (Table 4). To compare the effectiveness and implementation outcomes of the interventions, the Reach (how many and which type of patients were affected), Effectiveness (how many children took antibiotics and how many were managed with watchful waiting), Adoption (how many and which types of clinics participated), Implementation (fidelity, acceptability, appropriateness, time to implementation), and Maintenance (sustainability, feasibility of implementation in other sites) of interventions will be assessed. Contextual factors will be assessed at the child/parent, clinician, clinic, and health systems-levels. We will explore the differences in implementation effectiveness by patient population served, clinic type (pediatric, family medicine, urgent care), clinical setting (location, rurality, size), and organization. The fidelity, acceptability, and perceived appropriateness of the interventions among different clinician types, patient populations, and clinical settings will be compared.

**Table 4 Tab4:** Outcome Measures using RE-AIM

	**Project Questions**	**Outcomes**	**How will data be obtained and at what intervals? (Comparable/similar measures or tools may be substituted). Time frames are approximate**
Reach	• How many patients can be reached by the interventions?	• Number of AOM episodes	• Electronic health record (EHR) data (baseline, quarterly during intervention, post-intervention)
Effectiveness	• Do the interventions increase parent satisfaction? • Do the interventions reduce antibiotic use for AOM?	• % very or extremely satisfied • % children take antibiotic (yes/no)	• Parent surveys (0, 10 days after diagnosis, throughout intervention) • Parent focus groups (pre- and post-intervention)
Adoption	• How many clinics will adopt the interventions? • Do the interventions require adaptations to meet local needs?	• Number/proportion of eligible clinics that agree to participate • Characteristics of clinics that participate vs. clinics that opt not to participate • Number/proportion of enrolled clinics that implement all program components	• AC, DHHA, and IH health system data (pre-intervention, post-intervention) • Clinician and administrator surveys (post-intervention) • Key informant qualitative interviews (pre intervention)
Implementation	• How many clinicians participate in intervention components? • Are the interventions acceptable to clinicians? • How effectively is SDM^a^ used? • How many children are managed with watchful waiting v immediate prescription? • How many parents fill antibiotic prescriptions (even if not taken by child)?	• Implementation of intervention components and time to implementation • Use of program components (fidelity) - Education sessions - Feedback reports - EHR tools - Clinician champion - Meet CME program requirements • Clinician perceptions of intervention component utility, acceptability, and appropriateness • Parent perception of SDM and appropriateness • % managed by immediate antibiotic • % parents fill antibiotic prescription	• Stages of Implementation Completeness [47] (SIC) tracking (quarterly through the study) • Attendance at education sessions, meeting CME Requirements, proportion of AOM episodes where EHR tools were used, proportion of feedback reports read by clinicians- tracked using read receipts [48] (quarterly during intervention and post-intervention) • Clinician and administrator surveys using the acceptability of intervention measure (AIM) and intervention appropriate measure (IAM) (post intervention [34] • Focus groups of parents (pre- and post-intervention)
Maintenance	• What is the likelihood of sustainability of the interventions? • Do clinicians and administrators think it would be feasible to implement the interventions in other settings? • Could the interventions be implemented in other settings?	• Clinical Sustainability Assessment Tool (CSAT) Sustainability Score [49] • Feasibility of intervention (FIM) measure [50]	• Clinician and administrator surveys using CSAT and feasibility of intervention measure (FIM) [50] (post-intervention)

^a^
*SDM *Shared decision-making

### Stakeholder engagement

We will seek input from key stakeholders to guide this research, increase the likelihood of success of the interventions, and disseminate results of the trial. A stakeholder advisory council comprised of parents, clinicians, and clinic administrators with representation from AC, DHHA, and IH will be assembled. The council will meet quarterly during the first year of the study, and twice per year over the remaining study period. The initial focus of the council will be understanding participants’ experiences and perceptions of watchful waiting, the creation of parent-facing education materials that are culturally appropriate and acceptable, and discussion of potential adaptations to the interventions to increase likelihood of success. Subsequent sessions will focus on addressing obstacles in study implementation, interpretation of results, and dissemination of findings. A national stakeholder group comprised of AAP, CDC, and Pew Charitable Trusts has provided input into the study design and will assist with interpretation and dissemination of results, dissemination of resources and tools developed through this work, and incorporation of findings into recommendations and guidelines.

### Patient eligibility, enrollment, and data collection

Children aged 6 months-17 years old treated for uncomplicated AOM at a participating clinic during the study period will be prospectively identified. Trained research staff will contact the parents of potentially eligible children via telephone, electronic mail, or the EHR and screen for eligibility. Children who received any antibiotic within 30 days prior to the visit, have a history of tympanostomy tubes, have current tympanic membrane perforation, or have a concomitant diagnosis that may warrant an antibiotic (e.g., Group A streptococcal pharyngitis, pneumonia) will be excluded. For children meeting all eligibility criteria, informed consent will be obtained from the parents (with assent from the child when appropriate) by trained research personnel. An example of the informed consent form can be found in the Supplement. Upon enrollment, the parents will complete a survey where the following data will be collected: demographic characteristics of the child (age, sex, race, ethnicity, language preference, insurance type), vaccination status, and treatment strategy used at the visit (observation, delayed antibiotic prescription, or immediate prescription). Ten days after enrollment, the parents will complete a second survey assessing whether any antibiotics that were prescribed were ultimately filled and taken, clinical encounters occurring after the index visit, new antibiotics prescribed within 30 days after the index visit, and their satisfaction with their child’s care.

To prevent potential imbalances in the number of children enrolled from a given clinic, there will be maximum number of children that can be enrolled from each clinic each month. Furthermore, there will be enrollment targets for race/ethnicity, preferred language, and insurance status. Participant recruitment has not yet begun (Table 5).

**Table 5 Tab5:**
[figure not shown]
Detailed study timeline

To evaluate changes in antibiotic prescribing on a broader scale at the participating clinics, a secondary EHR analysis will be performed to determine the proportion of all children with an ICD-10 diagnosis of AOM meeting pre-specified eligibility criteria prescribed an immediate antibiotic (versus managed with observation or a delayed antibiotic prescription).

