## Methods

### Overview of study design

 This will be a pragmatic, cluster-randomized controlled trial that will use a hybrid implementation-effectiveness design [31]. The effectiveness and implementation outcomes of a “gold standard” [32] health systems-level intervention and a hybrid health systems-level plus shared decision-making intervention will be compared using the Practical Robust Implementation and Sustainability Model (PRISM) [33] and Reach Effectiveness Adoption Implementation Maintenance (RE-AIM) frameworks [34]. Participating clinics will be randomly assigned to one of the two interventions (Fig. 1) using covariate-constrained randomization. The primary outcomes of the study are 1) parent satisfaction with their child’s treatment for AOM, and 2) antibiotic courses *taken* by children with AOM by parent report. Secondary outcomes include 1) shared decision-making process and effectiveness [35, 36], 2) pediatric quality of life [14], 3) symptom severity and duration [22, 37, 38], 4) missed work, school, and daycare, 5) adverse drug events [14], 6) treatment failure [25, 39], 7) management strategy used (immediate antibiotic versus watchful waiting), and 8) whether or not an antibiotic prescription was filled at a pharmacy (Table 1).

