**Fig. 1 Fig1:**
[figure not shown]
Cluster-randomized trial design

**Table 1 Tab1:** Primary and secondary outcome measures

Outcome	Metric^a^	Data Source	Time of Measurement(s) (Days)
Co-primary outcomes			
Antibiotic Taken	% filled and took antibiotic (yes/no)	Survey	10
Parent Satisfaction	% very or extremely satisfied- Likert scale (7- point) Validated	Survey	10
Secondary outcomes			
Shared decision-making (Process measure)	Summed Score- Knowledge and Decisional Conflict Assessment. Shared Decision-Making Questionnaire (SDM-Q-9)	Survey	0
Pediatric Quality of Life	PEDS-QL Score	Survey	10
Symptom Severity and Duration	Likert scale (7-point) Validated [22, 37]- all ages AOM-Severity of Symptom scale [38]- age 6–35 months	Survey	0, 10
1. Symptom severity (max and day 10)	Above	Survey	0, 10
2. Time to symptom improvement	Above	Survey	0, 10
3. Time to all symptom resolution	Above	Survey	0, 10
4. Time to ear pain resolution	Above	Survey	0, 10
5. Symptoms resolved at day 10	Above	Survey	10
Missed Work, School, Daycare	# Days missed school/daycare # Days parents missed work	Survey	10
Adverse Drug Events	% with adverse drug event(s)	Survey	10
Treatment Failure	% changed management (took antibiotic if initially watchful waiting or new antibiotic if initially immediate antibiotic)	Survey and EHR^b^	10
Management Strategy Used (Process Measure)	% immediate antibiotic	EHR	0
Antibiotic Filled (Process Measure)	% filled antibiotic (even if not taken)	Survey	10

^a^A comparable tool or measure may be substituted

^b^*EHR* Electronic health record

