Implementation and sustainability infrastructure	• Current resources and resource utilization for AOM management (e.g., EHR-tools, education materials) and stewardship • Baseline workflow for AOM • Perceived facilitators/barriers to sustainability	• Key informant interviews (clinicians and administrators) • Process mapping interviews (clinicians and administrators)	• Adapt sustainability plan and EHR workflow • Develop workflow for SDM (Hybrid only)
Organizational characteristics	• Existing collaborations and information flow between clinics • Administrative support • Shared goals	• Key informant interviews (clinicians and administrators)	• Modify communication plan and add administrative support if needed
Patient characteristics	• Demographics • Urban, suburban, rural designation	• EHR data collection • Clinic zip codes	• Use data for covariate-constrained cluster randomization

^a^
*HEDIS* Healthcare effectiveness data and information set

Contextual factors will be assessed at the child/parent, clinician, clinic, and health systems-levels using key informant semi-structured interviews and focus groups, process mapping, and electronic health record (EHR) data. Semi-structured key informant interviews will be conducted with a convenience sample of clinic administrators and clinicians across participating clinics to understand 1) typical workflow of visits for children with AOM, 2) contextual factors that may facilitate or impede use of watchful waiting, 3) contextual factors that may facilitate or impede implementation of intervention components, and 4) organization culture. To understand parent perspectives of factors that may facilitate or impede the acceptance of watchful waiting, focus groups of a convenience sample of parents from each site will be conducted.

Finally, to better understand variability in care, assist with setting targets for improvement, and inform the randomization of clinics, baseline EHR data will be abstracted to evaluate pre-intervention antibiotic prescribing patterns and patient-level characteristics from potential participating clinics. Substantial efforts will be made to minimize missing data on predictors by abstracting data from multiple EHR locations. For missingness of key predictors, sensitivity analyses will be carried out using multiple imputation approaches [41].

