### Statistical analysis

The co-primary outcomes – whether the antibiotic was filled and taken and whether the parent was ‘very’ or ‘extremely satisfied’ with their child’s care – will be analyzed with a logistic mixed effects regression model. This model accounts for the hierarchical structure of the data with patients nested within clinics. The primary analysis will include covariates for the intervention group, the random effect for clinic, and pre-specified confounding factors including age, race, gender, ethnicity, language preference, and insurance type. Any variables that appear unbalanced between the study arms at *p* < 0.2 will also be included as predictors. Since it is possible that clinicians (within clinics) are another source of variation, an additional random effect for clinician within practices will be included if there is evidence of sufficient variability at this level. Multiple comparisons in testing the co-primary outcomes will be accounted for with an alpha = 0.025 to assess statistical significance. All other hypothesis tests will be two-sided with a significance level of 0.05.

Secondary outcomes (Table 1) will be analyzed using linear or logistic mixed effects regression, as appropriate. Similar random effects will be included accounting for the nested structure of the data. Secondary analysis results will be expressed as mean differences and regression coefficients or differences in proportion and odds ratios, as appropriate, with 95% confidence intervals (CIs).

Exploratory analyses will be conducted to test for potential effect modification by select patient characteristics. The effects of the health systems-level and hybrid interventions on antibiotic prescribing and parent satisfaction may differ based on race, ethnicity, insurance type, and clinical setting. Logistic mixed effects regression will be used including a main effect for the moderator and an interaction between the moderator and intervention variable. Due to the exploratory nature of these analyses, p-values will not be adjusted for multiple comparisons, however all subgroup analyses will be reported.

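### The clinic-wide EHR analysis is not tied to the by-arm model, and no model is said to use each clinic's baseline prescribing rate, which costs precision but not validity

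*Protocol article*

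**What the plan says.** The clinic-wide analysis appears at the end of the section on patient eligibility, enrollment and data collection, after the description of the consented survey cohort: "To evaluate changes in antibiotic prescribing on a broader scale at the participating clinics, a secondary EHR analysis will be performed". Its measure is "to determine the proportion of all children with an ICD-10 diagnosis of AOM meeting pre-specified eligibility criteria prescribed an immediate antibiotic", as opposed to observation or a delayed prescription. Neither arm is named and no baseline term is mentioned.

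Three other places bear on it.

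- **Table 1** lists Management Strategy Used as a secondary outcome: per cent immediate antibiotic, from the EHR, at day 0. The Statistical analysis section says "Secondary outcomes (Table 1) will be analyzed using linear or logistic mixed effects regression, as appropriate", and reports secondary results as "differences in proportion and odds ratios, as appropriate, with 95% confidence intervals".
- **The RE-AIM evaluation section** compares the interventions on, among other things, "how many children took antibiotics and how many were managed with watchful waiting".
- **The PRISM section** says "baseline EHR data will be abstracted to evaluate pre-intervention antibiotic prescribing patterns and patient-level characteristics", and gives informing the randomisation of clinics as one purpose.

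The covariates named for the primary model are age, race, gender, ethnicity, language preference and insurance type, plus any variable unbalanced between arms at p < 0.2. Similar random effects are promised for the secondary models. A clinic's baseline prescribing rate is not named for any model.

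**The concern.** Two things are left loose.

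First, the stated aim is to evaluate changes. Both arms receive the health systems-level package, and the hybrid arm adds the decision aid. A change over time pooled across clinics therefore has no untreated concurrent comparator and cannot be separated from secular trend. The trial's own question is the contrast between the two packages. The article has a by-arm model for the Table 1 outcome but does not say that the outcome is measured on all children with an ICD-10 diagnosis. If the Table 1 row covers only enrolled children, the by-arm model does not reach this dataset.

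Second, the clinic's own earlier prescribing rate is likely to be a strong predictor of its later rate. It is already being collected, yet it has no stated role in analysis. With only 33 clusters, variation between clinics limits precision, and a good cluster-level covariate is the cheapest way to reduce it.

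The dataset deserves this care. The survey cohort is expected to enrol 16% of eligible children, whereas the EHR analysis does not depend on parents agreeing to take part. It is the natural by-arm check on the survey results.

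**Working it through.** **The plan's own figures.** The article gives no power statement for the EHR analysis, so there is no stated figure to correct. The method used below (two proportions with design effect 1 + (m − 1) × ICC) was first tried on the survey sample size: 1,566 children, 33 clinics, m = 1,566/33 = 47.5, two-sided alpha 0.025, 80% power. The design effects are 1.93 (ICC 0.02) and 3.32 (ICC 0.05). The detectable differences for antibiotic taken, as increases from 12%, are 7.9 and 10.7 points, against the stated 8 and 11. For satisfaction, as increases from 76%, they are 8.6 and 11.0, against the stated 9 and 12 (the last is conservative). The method is close enough to the plan's to carry over.

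**Inputs for the EHR comparison**

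| Input | Value | Source |
|---|---|---|
| Clinics | 33 | Study setting and population |
| Clinics per arm | 16.5 | assumed 1:1 split |
| Children | 27,997 | Sample size and power, given there as the recruitment pool; its use here is an assumption |
| Children per clinic, m | 27,997/33 = 848 | arithmetic |
| ICC | 0.02 to 0.05 | Sample size and power (stated for the co-primary outcomes) |
| Two-sided alpha | 0.05 | Statistical analysis, for tests other than the co-primary ones |
| Power | 80% | as for the survey |
| Immediate-antibiotic rate, p | 50% | assumed |
| Between-period correlation of clinic rates, r | 0.5 or 0.7 | assumed |

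**Without baseline adjustment**

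Design effect = 1 + (m − 1) × ICC, which is 17.9 at ICC 0.02 and 43.4 at ICC 0.05. The effective total sample is then about 1,560 or 646 children.

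SE = √[2 × p(1 − p) × design effect / (16.5 × m)]

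- ICC 0.02: √[2 × 0.25 × 17.95 / 13,998] = 0.0253. Detectable difference = 2.80 × 0.0253 = 7.1 points.
- ICC 0.05: √[2 × 0.25 × 43.37 / 13,998] = 0.0394. Detectable difference = 2.80 × 0.0394 = 11.0 points.

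**With the clinic's baseline proportion as covariate**

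Multiply by √(1 − r²), which is 0.714 at r = 0.7 and 0.866 at r = 0.5.

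| | ICC 0.02 | ICC 0.05 |
|---|---|---|
| Unadjusted | 7.1 | 11.0 |
| r = 0.5 | 6.1 | 9.5 |
| r = 0.7 | 5.1 | 7.9 |

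**Sensitivity**

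- *Sampling error in clinic rates.* If r is the correlation of the true clinic rates, it is diluted by the reliability of the observed ones, m × ICC / design effect, which is 0.945 (ICC 0.02) or 0.978 (ICC 0.05). At r = 0.7 the detectable differences become 5.3 and 8.0 points.
- *Number of children.* Halving m to 424 moves the unadjusted figures only from 7.1 to 7.3 and from 11.0 to 11.1. The number of clinics governs precision, so the uncertain denominator hardly matters.
- *Assumed rate.* Solving numerically for a reduction from 70%, the range is 6.7 to 10.5 points unadjusted and 5.0 to 7.6 at r = 0.7. From 90% it is 4.7 to 7.6 and 3.4 to 5.3.
- *Cost of the covariate.* With t quantiles, the multiplier is 2.893 on 31 cluster-level degrees of freedom and 2.896 on 30. Spending one degree of freedom raises the detectable difference by about 0.1%. Using t in place of 2.80 raises every figure by about 3% and leaves the comparison unchanged.

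**The case against.** The strongest reply is that the arm comparison is already there. Per cent immediate antibiotic from the EHR is a Table 1 secondary outcome. Table 1 outcomes get mixed models with differences in proportion and odds ratios, and the RE-AIM section says the interventions are compared on watchful waiting. Enrolled parents report the treatment strategy by survey, yet Table 1 takes this outcome from the EHR, which fits the view that the row and the clinic-wide analysis are the same thing. Nothing says that the arms will be pooled, and evaluating changes states a purpose without defining an estimator. Most of this stands. What it leaves open is whether the row covers all ICD-10 children or only enrolled ones.

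A reader might infer that the plan has no comparison by randomised arm, or that these data cannot show which intervention works better. The documents support neither. The first overlooks Table 1 and the Statistical analysis section. The second is false because every clinic is randomised, so the same records support a valid contrast with or without a baseline covariate. Nor should about 28,000 be taken as the stated size of the EHR analysis: it is the pool for survey recruitment, and after clustering it is worth some 650 to 1,560 independent children.

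It can also be said that baseline data do have a role, since they inform the randomisation, and that a condensed article may leave the model for a secondary analysis to the full protocol or SAP. Both are fair and keep this point small. But using the baseline rate in the design does not recover its precision in the analysis. The p < 0.2 imbalance rule is least likely to bring the rate into the model if the randomisation has balanced it, even though it would remain prognostic.

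**Conclusion.** The point holds as a clarification with a concrete gain in precision. It is not an error that invalidates an analysis. The clinic-wide EHR analysis is framed as a change and is not tied to the by-arm model, and the baseline prescribing rate is collected without a stated place in any model. Under the assumptions above (1:1 split, 50% rate, 848 children per clinic, ICC 0.02 to 0.05), adjustment lowers the detectable difference between arms from about 7 to 11 points to about 5 to 8 at r = 0.7. That is a reduction of roughly a quarter to 29%, depending on whether sampling error in the clinic rates is allowed for. At r = 0.5 it falls to about 6 to 9.5 points. The rate, r, the split and the denominator are not in the documents. The size of the gain depends mainly on r, which could only be estimated from clinic rates in more than one period.

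**What to change.** State that the proportion given an immediate antibiotic among all eligible ICD-10 children in the intervention period is compared between randomised arms, using the logistic mixed model of the Statistical analysis section with a random effect for clinic and each clinic's baseline immediate-antibiotic proportion as a covariate. Say in Table 1 or its footnote whether Management Strategy Used refers to this population, to enrolled children, or to both. Report any before-after change pooled across arms as descriptive only.

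The cost is one or two sentences and one cluster-level degree of freedom out of 31. The article already plans to abstract the baseline data and says that recruitment has not begun, so no new data collection is needed.
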